## Abstract

**Background:**

Chronic musculoskeletal pain and depression are very common in primary care patients. Furthermore, they often appear as comorbid conditions, resulting in additive effect on adverse health outcomes. On the basis of previous studies, we hypothesise that depression and chronic musculoskeletal pain may benefit from an integrated management programme at primary care level. We expect positive effects on both physical and psychological distress of patients.

**Methods:**

*Objective:* To determine whether a new programme for an integrated approach to chronic musculoskeletal pain and depression leads to better outcomes than usual care.

*Design:* Cluster-randomised controlled trial involving two arms: a) control arm (usual care); and b) intervention arm, where patients participate in a programme for an integrated approach to the pain-depression dyad.

*Settings:* Primary care centres in the province of Tarragona, Catalonia, Spain,

*Participants:* We will recruit 330 patients aged 18–80 with moderate or severe musculoskeletal pain (Brief Pain Inventory, average pain subscale ≥5) for at least 3 months, and with criteria for major depression (DSM-IV).

*Intervention:* A multicomponent programme according to the chronic care model. The main components are care management, optimised antidepressant treatment, and a psychoeducational group action.

*Blind measurements:* The patients will be monitored through blind telephone interviews held at 0, 3, 6 and 12 months.

*Outcomes:* Severity of pain and depressive symptoms, pain and depression treatment response rates, and depression remission rates.

*Analysis:* The outcomes will be analysed on an intent-to-treat basis and the analysis units will be the individual patients. This analysis will consider the effect of the study design on any potential lack of independence between observations made within the same cluster.

*Ethics:* The protocol was approved by the Research Ethics Committee of the Jordi Gol Primary Care Research Institute (IDIAP), Barcelona, (P14/142).

**Discussion:**

This project strengthens and improves treatment approaches for a major comorbidity in primary care. The design of the intervention takes into account its applicability under typical primary care conditions, so that if the programme is found to be effective it will be feasible to apply it in a generalised manner.

**Trial registration:**

ClinicalTrials.gov: NCT02605278; Registered 28 September, 2015.

## Background

Pain and depression are common and relevant conditions in primary care patients [1, 2]. At this level of care 40 % of visits are related to pain, and musculoskeletal ailments represent the principal chronic pain disorders, particularly lower back pain and joint pain [3–5]. Major depression is present in 14 % of all primary care patients [6] and most of them (up to 85 %) also report pain-related symptoms [7, 8].

When depression and pain co-occur, both disorders can have an additive adverse effect on health and its management: the pain increases the complexity in the treatment of depression and interferes with recovery, while depression has a similar effect on the therapeutic response for the pain [9, 10].

Treatment of individuals with chronic pain and depression is complex. For example, antidepressants, which are a well-established and effective treatment for depression, have also been used for musculoskeletal pain disorders but the evidence for their usefulness when applied in this way is controversial [11]. Care management programmes for depression have shown promising results to improve the clinical outcomes in depressed patients [12], and that interventions are effective and feasible within our healthcare system [13, 14]. In turn, psychoeducational programmes and programmes supporting self-management of pain have shown to be somewhat effective for lower back and joint pains, with additional benefits on psychological distress [15]. Although of potential interest, these treatment programs are often difficult to apply in primary care, mostly because their broad format and complex execution negatively affect their feasibility in that setting [16, 17].

It therefore seems that a strategy for the joint management of chronic pain and depression is a reasonable option that could be expected to produce a synergistic effect on clinical outcomes. Based on this premise, in a study performed in primary care settings Kroenke et al. developed and tested a programme that integrated optimised antidepressant therapy (actively managed by a nurse care manager) and a psychoeducational behavioural intervention for pain self-management. There was evidence for substantial improvement in the depression symptoms as well as moderate improvements in the pain and the functional interference they were causing [18]. However, this efficacy and usefulness documented in United States health settings have not been investigated in other locations.

Our hypothesis is that both depression and chronic musculoskeletal pain will benefit from an integrated management programme for pain-depression comorbidity, established at the primary care level in our health system. Positive effects can be expected, with regard to the physical as well as psychological adjustement of patients.

## Methods/design

### Aim

The general objective is to study whether a programme to manage chronic musculoskeletal pain and depression in primary care results in better outcomes when compared to those achieved through the usual approach. The specific objectives are to determine, over the course of a 12-month monitoring period, the effectiveness of this programme on depression severity, pain severity, and therapeutic response rates for pain and depression.

### Design

A controlled trial will be conducted involving a random assignment of clusters (patients registered with the same primary care physician) to two study groups: a) control group undergoing usual care; and b) treatment group, where participants will undergo a program for the integrated management of chronic pain and depression (Fig. 1).

**Fig. 1 Fig1:**
[figure not shown]
Flowchart: sampling, recruitment, randomization and monitoring of patients

### Setting and study sample

The study will be conducted at the Institut Català de la Salut (Catalan Health Institute) primary care centres in the province of Tarragona, Catalonia, Spain.

Patients will be selected from the rosters of the participating physicians using the following inclusion criteria: aged 18 to 80 years old, experience moderate or severe musculoskeletal pain (average pain intensity scale on the Brief Pain Inventory (BPI) scale ≥ 5 points) for at least three months despite analgesic treatment, and have diagnostic criteria for major depressive episode (DSM-IV).

The following patients will be excluded: those suffering from any physical, psychological, or language-related limitation, or any concurrent illness that impedes their comprehension or participation in the evaluations; patients with a psychotic disorder, bipolar disorder, or alcohol or drug dependencies; and patients who are pregnant or lactating. Also considered as ineligible will be patients with an established diagnosis of fibromyalgia or somatization disorder; those with a workplace disability claim currently in progress; and those expecting an intervention for a joint prosthesis during the next 12 months. If a patient is being treated with antidepressants, this will not be a criterion for exclusion as long as the patient shows major depression criteria at the time of entering into the study.

### Random assignment to the study groups

To avoid potential contamination between the intervention and usual care, which could take place if the same physician were attending patients from the intervention group and the control group, the patients will be assigned to the study groups by clusters, with each cluster comprising patients belonging to the same physician’s roster.

The clusters from each primary care centre will be assigned to either the intervention group or control group by someone not otherwise involved in the study ([name], Spanish Society of Family and Community Medicine), following a simple randomised procedure using the List Randomiser tool at www.random.org. The physicians will commit to participate in the study prior to this assignment, and the patients will accept their recruitment without knowing which study group they will be assigned to.

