### Statistical methods

#### Sample size

We will consider the response rates to treatment for depression and pain as reference variables. We will assume that the proportion of patients achieving a therapeutic response will be 50 % for both outcomes in the control group [14], and we expect a difference ≥17 % in the intervention group. Accepting an alpha risk of 0.05 and a beta risk of 0.2 in a two-tailed test, and with an expected loss of 15 %, 154 subjects are enough for each group. We will use the following formula to correct this figure for the design effect (randomisation by clusters): Deff = 1 + (m - 1) × ICC, where Deff: design effect; m: cluster size; and ICC: intraclass correlation coefficient [41]. Assuming an ICC of 0.01 [14] and m = 8, the Deff will be 1.07. As such, each study group will require 165 patients (1.07 × 154 = 165), distributed into 21 clusters of 8 patients each.

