#### Analysis strategy

The randomisation will take place at the level of the primary care physicians (clusters), while the results of the intervention will be analysed at the individual-patient level [41]. The principal analyses will be by intention-to-treat, considering the patients from each group according to the initial assignment to the study groups, independently of compliance with the programme by either the individual patient or the physician.

We will compare the intervention group with the control group in order to verify that they are comparable in their baseline characteristics.

The main outcomes (dependent) variables are depressive symptoms (HSCL-20 score), response rate to the depression treatment, remission rate for depression, severity and interference of the pain (BPI), therapeutic response rate for the pain, and health-related quality of life at 3, 6, and 12 months.

In order to evaluate the effects of the intervention on the dichotomous variables we will use multilevel logistical regression models with mixed effects, adjusted by cluster, and employing an estimation of the Odds Ratio (95 % CI) of the intervention group with respect to the control group as a measurement of the effect. In order to measure the effect on the continuous variables we will use linear regression models with random effects (cluster), estimating the differences in adjusted averages (95 % CI) for the intervention group versus control group. For the main outcome variables we will calculate the intracluster correlation coefficient (ICC). Statistical significance will be established as *p <* 0.05. We will use STATA-12 and SPSS v.15 software for these calculations. This analysis strategy takes into account the design effect (randomisation by clusters) for any potential lack of independence among observations within the same primary care centre.

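### Simple allocation of about 42 physician clusters, with no stated split rule or balance by centre, does not secure 21 clusters per arm or both arms in each centre; the cost is a modest loss of precision

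*Protocol article*

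**What the plan says.** Under *Random assignment to the study groups*, the unit of allocation is the physician, "with each cluster comprising patients belonging to the same physician’s roster". On the method, the section says: "The clusters from each primary care centre will be assigned to either the intervention group or control group", by someone outside the study, "following a simple randomised procedure using the List Randomiser tool". It gives no allocation ratio, block or stratum, and no rule for turning a shuffled list into two arms. Physicians commit before assignment, and patients accept recruitment without knowing their group.

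*Sample size* sets 165 patients per arm, "distributed into 21 clusters of 8 patients each". That makes 42 clusters in all.

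*Analysis strategy* adjusts for cluster as a random effect and names no centre term. It closes by saying that the strategy handles "any potential lack of independence among observations within the same primary care centre", although the randomised cluster is the physician and not the centre.

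**The concern.** Simple randomisation is the name of a method that guarantees neither equal arms nor both arms in every stratum. With only about 42 units, chance imbalance in cluster numbers and in centre mix is likely. The sample size assumes equal arms, and the analysis section itself treats dependence within a centre as something to be handled. Yet no allocation rule is stated that balances on centre, and no model term is named that represents it.

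A centre whose physicians all fall in one arm contributes no within-centre comparison, and later adjustment cannot supply one. At stake is precision in a design with about 80% power and little slack.

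**Working it through.** **1. The plan's own figure.** Inputs from *Sample size*: "the proportion of patients achieving a therapeutic response will be 50 % for both outcomes in the control group"; "we expect a difference ≥17 % in the intervention group"; two-sided alpha 0.05; power 80%; loss 15%; ICC 0.01; m = 8.
- Two proportions, 0.50 v 0.67, pooled variance: 131 per arm; 131/0.85 = 154.1, rounded up to 155. The arcsine formula gives 130.4/0.85 = 153.5, hence 154 as stated.
- Deff = 1 + 7 × 0.01 = 1.07; 154 × 1.07 = 164.8, hence 165; 165/8 = 20.6, hence 21 clusters.

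The stated size reproduces.

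**2. Cluster split under the literal reading.** Number in one arm ~ Binomial(42, 0.5), an assumption about what simple means here.
- P(21:21) = C(42,21)/2^42 = 12.2%.
- P(outside 18 to 24) = 28.0%.
- P(16:26 or worse) = 16.4%.

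**3. Power by split.** Effective patients per cluster = 8 × 0.85/1.07 = 6.36.

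| Split | Power (range: which arm is smaller) |
|---|---|
| 21:21 | 80.8% |
| 18:24 | 79.9–80.2% |
| 16:26 | 78.3–78.8% |
| 14:28 | 75.8–76.5% |

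Averaged over the binomial, expected power is 79.9%, a loss of about 1 point. In variance terms, the mean of (1/n1 + 1/n0) divided by 2/21 is 1.026, so the expected variance is about 2.6% above plan.

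**4. Centres wholly in one arm.** The probability is 2 × 0.5^k for k physicians per centre. The number of centres is not given, so k is an assumption: 50% for k = 2, 25% for k = 3, 12.5% for k = 4, 3.1% for k = 6.

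**5. What balance on centre would save.** Patients of one physician also share a centre, so any centre component c is part of the stated ICC of 0.01. The variance of a physician-cluster mean, in units of total variance, with 8 × 0.85 = 6.8 patients observed, is

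0.01 + 0.99/6.8 = 0.1556.

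Equal allocation within even-sized centres removes c from the variance of the arm difference, so the saving is c/0.1556.

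| Share of the ICC between centres | c | Saving |
|---|---|---|
| a quarter | 0.0025 | 1.6% |
| a half | 0.005 | 3.2% |
| all | 0.01 | 6.4% |

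Odd-sized centres keep part of the term. With 3 physicians in each of 14 centres and 21:21 overall, what remains is 14 × (1/21)² = 0.032, against 2/21 = 0.095 without balance. A third stays, so the savings fall to 1.1%, 2.1% and 4.3%.

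**The case against.** The strongest reply is that clustering is already paid for. Deff 1.07 is built on the total ICC of 0.01, and any centre component lies inside it. Under independent assignment the terms shared by physicians of the same centre average about zero in the arm difference. A reader might infer that simple allocation adds a centre penalty on top of the planned variance, or might try a centre ICC of 0.02. The documents support neither: the planned variance already holds the centre part, and 0.02 exceeds the stated total. This stands. Only the small arm-size effect lies above plan, and balance on centre is a gain below plan.

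A reader might also infer that centre differences bias the treatment comparison. They do not: randomisation keeps the contrast unbiased in expectation, and chance imbalance acts through variance.

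Next, the text does not describe independent coin tosses. A tool that orders a list, applied to the clusters of each centre, may mean one list per centre divided between the arms, and the planned 21 per arm fits a divided list. So it cannot be said as fact that there was no balance within centre. But no equal split is stated, the word simple points the other way, and one pooled list cut in half would fix the arm totals without fixing the centre mix. If lists were made per centre, centre belongs in the models, so the text still needs a change.

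Finally, *Trial Status and forecast execution dates* reports 130 of 330 patients recruited in February 2016. How many clusters were still unallocated is unknown, so the change to allocation may reach only a few of them. The model term is open in any case.

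**Conclusion.** The point holds as a modest matter of design efficiency and clarity, and it is worth correcting because correction is cheap. As written, the allocation does not secure the equal arms that the sample size uses, nor both arms in each centre. The loss is about 1 point of expected power, plus a forgone variance saving of up to about 6% if all of the stated ICC lies between centres, or about 1–3% if a quarter to a half does.

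These figures rest on three assumptions: independent 1:1 assignment of 42 clusters, an unknown number of physicians per centre, and an unknown centre share of the ICC. Validity of the comparison is not in question. Separately from these figures, the sentence on dependence within a centre does not match a model whose only named grouping is the physician cluster.

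**What to change.** - **Allocation.** For clusters not yet allocated, shuffle the committed physicians within each centre and split the list equally between arms. The same independent person draws any odd place at random. Keep allocations already made. If this is what was done from the start, say so and drop the word simple.
- **Analysis.** Add a centre term to the linear and logistic models, for example a random centre effect above the physician cluster, so that the statement about dependence within a centre becomes true.

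The cost is one sentence on allocation and one model term. The downside is that the last physician in a centre becomes predictable. That matters little, because physicians commit beforehand, patients accept recruitment unaware of their group, and an outsider allocates. Arm totals may still differ slightly through the odd places.

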### The multicomponent program: basic characteristics

The intervention consists of a programme that integrates and organises several components, designed according to the basic premises of the chronic care model [19] including the following main components:

#### Optimised management of major depression

Depression will be managed based on the algorithms and recommendations of the comprehensive clinical guide in the computerised primary care clinical records. This is a computerised system used to support clinical decisions that has been developed based on the most recent clinical practice guidelines for major depression [20, 21]. It assists physicians with decisions regarding diagnosis, treatment, and monitoring of major depression; systems for recording and retrieving information on a patient’s clinical status; and automated alerts for clinical situations showing poor control of the illness or risk factors [22].

#### Care management

The care manager is a psychologist who, based on the algorithms and recommendations from the computerised guideline, will support and collaborate with the treating physician in managing the patient, while also providing support for suitable compliance with the treatment by the patient and preventing discontinuities in the care. The care manager will also participate in the monitoring of the patients. Periodic follow-up will be carried out by telephone. Typically, these phone contacts will occur monthly during the first two months of the study, then every other month after that. The content of the telephone contact is structured and includes: monitoring of symptoms with the PHQ-9 (Patient Health Questionnaire) scale, the MINI scale for suicide risk (Mini International Neuropsychiatric Interview), and the GAF scale (Global Assessment of Functioning) to evaluate the impact of the depression on the patient’s functioning; as well as evaluating the patient’s compliance with treatment and identifying any difficulties in this area. These contacts will also provide the patients with therapeutic advice and reminders about upcoming visits.

On the basis of the information available through the computerised system, the care manager will provide the treating physician with information that will allow him or her to take the best decisions about health care. The care manager will also collaborate with the attending physician to ensure that these decisions (treatment, psychoeducation, referrals, new visits, etc.) are taking place effectively. Supervision and approval of this activity will be performed on a weekly basis by an expert member of the research team.

#### Psychoeducational intervention programme for patients with chronic pain and depression

This is a group-based psychoeducational programme with a cognitive-behavioural orientation. It promotes understanding and self-management of depression and pain as well as the related difficulties, in order to facilitate the acquisition of adaptive strategies for managing these conditions on a day-to-day basis and provide incentives for the patient to play an active role in their illness management [23, 24].

The programme is structured into 9 weekly sessions of 2 h, led by the care manager. These sessions include a presentation of the content and dialogue, as well as interaction between the participants. In order to promote the active and independent role of the patient, “homework” is assigned after each session, which will be reviewed at the beginning of the following session. The content of the psychoeducational sessions covers the following areas: understanding of pain; managing emotions; basic relaxation techniques; cognitive restructuring strategies; problem solving; establishment of life goals; relationships between pain and physical activity, healthy postures, and sleep; maintenance of the strategies learned; and preparation of plans to be applied in the event of temporary setbacks.

In order to facilitate the sessions, a teaching manual is made available along with other supporting materials (slide-based presentations, brochures, and forms).

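### Group sessions run in the intervention arm only, but sample size and models allow only for physician clustering: stated power is optimistic, and standard errors are too small if groups mix physicians' patients

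*Protocol article*

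**What the plan says.** The section on the psychoeducational programme describes the component this way: "This is a group-based psychoeducational programme with a cognitive-behavioural orientation". It has nine weekly 2-hour sessions led by the care manager, with dialogue and interaction among participants. The Usual care section leaves control patients to their physicians' own judgement and gives them no study-run groups.

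The Design section specifies "random assignment of clusters (patients registered with the same primary care physician) to two study groups". The Sample size section builds its correction from that unit alone, using Deff = 1 + (m - 1) × ICC, "where Deff: design effect; m: cluster size; and ICC: intraclass correlation coefficient". With m = 8 and ICC = 0.01 it obtains 1.07 and applies it to both arms.

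The Analysis strategy section identifies the clusters as the primary care physicians. Dichotomous outcomes get a mixed-effects logistic model adjusted by cluster. Continuous outcomes get "linear regression models with random effects (cluster", the bracketed word being the only random term named. Its closing sentence says the approach deals with dependence within a primary care centre. Neither section mentions the session group.

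**The concern.** Patients who share nine interactive sessions may end with more similar outcomes than patients who do not. That correlation is created by the treatment, exists in one arm, and need not follow physician rosters. The protocol accepts that dependence between patients must be allowed for, then allows only for the dependence that comes from randomising physicians.

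Two things are at stake. First, the intervention arm carries less information than a design effect of 1.07 implies, so the stated power is too high. Second, if a session group draws from several physicians, a physician random effect captures only part of the group variance and is shared across both arms. The standard error of the treatment effect is then too small and the test rejects too often.

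The assumed ICC of 0.01 does not settle the matter. It is taken from a source that the Background cites with care management programmes for depression, while psychoeducational programmes are described separately. Nothing in the article shows that 0.01 includes correlation from shared sessions.

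**Working it through.** **Inputs from the Sample size section.** Control response: "the proportion of patients achieving a therapeutic response will be 50 % for both outcomes in the control group". Effect: "we expect a difference ≥17 % in the intervention group", so 50% against 67%. Error rates: "Accepting an alpha risk of 0.05 and a beta risk of 0.2 in a two-tailed test". Loss: "with an expected loss of 15 %, 154 subjects are enough for each group". Deff 1.07; 165 per arm.

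**Reproducing the plan's figure.** The pooled two-proportion formula without continuity correction gives 131 per arm. 131 / 0.85 = 154.1, which rounds up to 155 (stated 154). 1.07 × 154 = 164.8, so 165. Evaluable: 165 × 0.85 = 140.25 per arm. The stated figure follows from its inputs.

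**Assumed inputs.** Group size g and group ICC are not in the article. I take g = 10 and ICC from 0.01 to 0.10.

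**Power, groups mixing rosters.** The control Deff stays at 1.07. For the intervention arm, Deff_int = 1.07 + (g - 1) × ICC_group. Then

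SE = √[(0.50 × 0.50 × 1.07 + 0.67 × 0.33 × Deff_int) / 140.25], and power = Φ(0.17 / SE - 1.96).

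With no group effect, SE = √(0.50408 / 140.25) = 0.05995 and power = Φ(0.876) = 80.9%. With g = 10:

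| Group ICC | Deff_int | SE | Power |
|---|---|---|---|
| 0.01 | 1.16 | 0.0611 | 79.4% |
| 0.02 | 1.25 | 0.0623 | 77.9% |
| 0.05 | 1.52 | 0.0656 | 73.6% |
| 0.10 | 1.97 | 0.0708 | 67.0% |

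With a pooled variance under the null, the base is 80.1% and the four values are 78.5%, 76.9%, 72.3% and 65.3%. These powers assume an analysis whose standard error reflects the group correlation.

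**Power, one roster per group.** Physician and group then coincide. With m = 8, Deff_int = 1 + 7 × (0.01 + ICC_group) = 1.14, 1.21, 1.42 and 1.77. Pooled-variance power is 78.9%, 77.6%, 73.9% and 68.3%, so power falls here as well.

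**Type I error.** If the model captured none of the group variance, the ratio of true to model SE would be √[(1.07 + Deff_int) / (2 × 1.07)]. For g = 10 and ICC 0.05 this is √(2.59 / 2.14) = 1.100, and type I error is 2 × [1 - Φ(1.96 / 1.100)] = 7.5%. The same formula gives 6.0% at ICC 0.02 and 10.0% at 0.10. A physician effect captures some of the variance, so simulation gives lower figures. The set-up was 21 physicians per arm, 7 analysed patients each, groups mixing three physicians of a centre, a t-test on physician means with 40 df, and 20,000 trials per cell.

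| Arrangement | ICC 0.02 | ICC 0.05 | ICC 0.10 |
|---|---|---|---|
| Mixed groups of 10, all attend | 5.7% | 6.6% | 8.3% |

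Over the same three ICCs, mixed groups of 21 give 6.5% to 11.6%, mixed groups of 10 with 70% attendance give 5.4% to 6.7%, and groups holding one physician's patients give 4.8% to 5.2%. The last range is the nominal level within simulation error (standard error √(0.05 × 0.95 / 20,000) = 0.15 points).

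**The case against.** A reader might infer that the planned intervals are too narrow and that type I error exceeds 5% whatever happens. The documents do not support that. They do not say how session groups are formed. A physician cluster of 8 is a plausible session-group size, and if one roster forms one group, the physician effect absorbs the group correlation and type I error is preserved. This objection stands and makes the standard-error part conditional.

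Three further points limit the size. The analysis is by intention to treat, and the Discussion expects some patients to be weakly motivated for the sessions. Non-attenders share no group effect, so inflation shrinks. The only ICC in the article is 0.01, at which the power loss is 1 to 2 points, and manual-based content could keep differences between groups small. Nothing in the article supports 0.05 or 0.10 specifically. The simulation also used physician means as a stand-in for the planned mixed models.

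The closing sentence of the Analysis strategy section mentions the primary care centre. If that meant a centre-level term, it would absorb part of the correlation from groups formed within a centre. But the cluster is defined in the same section as the physician, and no centre term is specified.

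It can also be said that a condensed article leaves such detail to the analysis plan. Group size and formation may well sit there. The design effect and the random term, however, are fixed in this text, and as fixed they leave out the session group.

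**Conclusion.** The point holds in conditional form. Group delivery in one arm, a common design effect of 1.07 and a physician-only cluster effect are all in the text. For any positive session-group correlation the stated 80% power is optimistic under either way of forming groups. The loss is 1 to 2 points at an assumed ICC of 0.01 and reaches about 13 to 14 points (80.9% to 67.0%) at 0.10 with groups of 10. Standard errors are too small only if groups mix physicians' patients, which the documents neither state nor exclude. Type I error is then about 5.7% to 8.3% over ICC 0.02 to 0.10 for groups of 10 with full attendance, and lower with partial attendance. The direction is firm under these conditions. The size rests on assumed group size, ICC and attendance. The arithmetic leading to 165 per arm is not itself in error.

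**What to change.** - **Data.** Record a session-group identifier for every intervention patient. Use the group allocated, whether or not the patient attended, and treat any patient never allocated to a group as a singleton. The article reports 130 of 330 recruited in February 2016, so the identifier can be recorded prospectively for the remainder.
- **Analysis strategy section.** Keep the physician random effect in both arms and add a session-group random effect in the intervention arm only, crossed with physician where groups mix rosters. Name the physician-only model as the fallback if the binary model does not converge.
- **Sample size section.** State that 80% power is conditional on no session-group correlation, and show power over a range of group ICC such as 0.01 to 0.10. Enrolment does not change.

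The cost is one data field, slightly wider intervals, a less favourable stated power, and possible convergence difficulty in the crossed logistic model when there are few groups. Treatment, randomisation and visits are unaffected.
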